#### 8.1.2 Secondary study parameters/endpoints (if applicable)

Operative (i.e. injury of spermatic vessels or spermatic cord, tuba lesions, bleeding and apnea) and postoperative complications (i.e. hematoma/scrotal edema, hydrocele, wound infection, iatrogenic ascent of the testis, testicular atrophy and ileus) within one year after primary surgery.

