Percutaneous Internal Ring Suturing (PIRS) technique is the least invasive laparoscopic technique that uses extra-corporeal suturing and has a similar complication rate to other laparoscopic techniques. Therefore, PIRS is the most preferable technique. The PIRS technique requires only one umbilical port and a puncture point access through were the suture is placed. In contrary to intra-corporeal laparoscopic techniques, the PIRS technique does not require intra-abdominal suturing, which is time consuming, has a high learning curve and carries a higher risk for iatrogenic visceral injury following the many manipulations with instruments in the peritoneal cavity (8, 9). In conclusion, the PIRS technique leads to visualization of the peritoneal cavity without leaving any scars and is a safe laparoscopic

hernia repair technique, even if it is performed by a surgeon with a basic skill level in endoscopic surgery (8, 10).

Several randomized controlled trials comparing laparoscopic with open paediatric hernia repair have been published, but many outcome parameters have not been addressed which include among others some peri- and post-operative complications (such as apnea, ileus) and health care costs (11). Furthermore, there is no current randomized controlled trial comparing open and laparoscopic PIRS technique. Consequently, there is an ongoing debate about the best treatment strategy and decisive evidence on the superiority of one of either treatment strategies is lacking. The aim of this randomized controlled trial is to provide an extensive comparison for effectiveness and a cost-effectiveness analysis of laparoscopic PIRS technique compared to open hernia repair in infants aged 0 months to 16 years of age with a primary inguinal hernia.

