## 5. TREATMENT OF SUBJECTS

### 5.1 Investigational product/treatment

Laparoscopic hernia repair will be performed according the PIRS technique by Patkowski et al (8). This approach will be done under general anaesthesia with muscle relaxation. The patient will be placed in supine position. The operation is as follows: Pneumoperitoneum is established by introducing a 3-5-mm reusable trocar through a sub-umbilical incision. Insufflation pressure is between 8–10 mm Hg. A 30-degree telescope is used and the whole peritoneal cavity is inspected. Any hernia is reduced manually or with the aid of the telescope tip. The location for the needle puncture is assessed by pressing the inguinal ring region from the outside with the tip of a Kocher or any other blunt surgical instrument. Under laparoscopic-guided vision the 16 or 18 gauge injection needle with nonabsorbable thread inside the barrel of the needle is introduced into the body, through the abdominal wall into the abdominal cavity. Needle movement is performed on the outside of the body under laparoscopic vision. With the movements of the tip of the needle the thread passes under the peritoneum, over half of the internal ring including a part of the ligament and adjacent tissue. The thread is pushed through the barrel of the needle into the abdominal cavity and eventually makes a loop. The needle is pulled out, leaving the loop of the thread inside the abdomen. From outside the patient's body, one of the thread ends is introduced again into the barrel of the needle and the needle passes through the same skin puncture point, to surround the other half of the internal ring with part of the round ligament. To prevent the vas deferens and testicular vessels from injury a small space is left above these structures. The end of the thread goes through the barrel of the needle into the thread loop and the needle is withdrawn. Next, the thread loop is pulled out of the abdomen with the thread end caught by the loop. In this way the thread is placed around the inguinal ring under the peritoneum and both ends exit the skin through the same puncture point. The knot is tied to close the internal ring and is placed under the skin. If a contralateral hernia or CPPV is found, it is closed during the procedure according to the same method as described above, regardless of its diameter. The umbilical wound is closed with absorbable stitches and covered with pressure dressing to prevent hematoma formation. The skin puncture point in the inguinal region is left without any dressing.

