
## **5.2 Use of co-intervention (if applicable)**

Open hernia correction is as follows: an incision is made in a skin line in the groin. The incision is carried down through the dermis to expose subcutaneous fat and Scarpa fascia. The Scarpa fascia is cut to expose the external oblique muscle. According to the surgeons' preference and/or opinion the external oblique is incised. The hernia sac is searched and if a hernia or PPV is absent, the procedure is finished by closure of Scarpa fascia and skin. If a hernia or PPV is found, the hernia is grasped and cord structures are elevated, creating an opening underneath the sac. An instrument is placed through the opening. Vas deferens and vessels (in boys) are dissected away from the hernia sac or PPV. The sac is then checked for contents. The sac is divided. The proximal sac is then cleaned to the level of the internal inguinal ring, twisted on itself and ligated at the level of the internal ring. The testis (in boys) is returned to the normal scrotal position. Scarpa fascia is closed with a suture. Skin is closed. During the open repair, no contralateral exploration will be performed in the case of a unilateral inguinal hernia.

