#### Definitions

*Testicular atrophy*: Complete testicular atrophy: no palpable testicular tissue in scrotum.

*Partial testicular atrophy*: Testis documented to be smaller at follow-up than at time of inguinal hernia repair.

*Wound infection/Surgical site infections*: Infection, occurring within 30 days of surgery, involving only the skin and subcutaneous tissue. Purulent discharge or organisms isolated from aseptically obtained wound culture must be present. Also at least one of the following signs of infection must be present: Pain or tenderness, localized swelling and redness or heat.

*Apnoea*: An unexplained episode of cessation of breathing for 20 seconds or longer, or a shorter respiratory pause associated with bradycardia, cyanosis, pallor, and/or marked hypotonia.

Total duration of surgery (including anaesthesia) related to primary open or laparoscopic inguinal hernia repair.

Postoperative pain measured according to the children and infants post-operative pain score (CHIPPS) and VAS and pain medication requirement related to post-operative pain within 2 weeks after primary operation.

Length of hospital stay related to inguinal hernia within one year after primary operation.

Time to full recovery within one year after primary operation.

CPPV rate during laparoscopic contra-lateral exploration in the PIRS group. When seen, the CPPV will be corrected.

MCIH rate within one year after primary operation.

Cosmetic appearance scored on a 5-Likert scale from 1-5 (1= bad, 2=unsatisfactory, 3=satisfactory, 4=good, 5=excellent) within one year after primary operation. Cosmetic appearance will be scored 4 weeks and 1 year after primary surgery.

Cost-effectiveness will be assessed from a societal and health care perspective and will include cost of surgery, hospitalization, control visits, re-operation, complications and loss of productivity of the parents/caretakers. Most data will be registered in the medical records; specific data entry forms will be used. Data on productivity loss will be collected by online questionnaires before surgery, four weeks after surgery, one year after surgery and in case of a recurrence or MCIH, four weeks after re-operation. Cost of the operation will be measured using a bottom-up micro costing approach. Other costs will be valued using guideline prices.

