#### Assessment of study parameters/endpoints

The following applies to all infants admitted to the hospital for inguinal hernia repair included in this study.

Preoperative size of both testes, the number of operations per infant, length of hospital stay, total duration of operations (including anaesthesia) and perioperative complications of surgery (iatrogenic injury, apnoea) will be recorded in Case Report Forms by the (fellow) paediatric surgeon. One telephone call is performed by a member of the research team after four weeks in the control and intervention group to obtain information regarding recovery of the patient, wound healing and recurrence. Pre-operative and four weeks and one year post-operative, parents or patients older than 12 years of age (with the aid of their parents) will fill out an online questionnaire regarding health of the subject and cost-effectiveness. Invitations for the questionnaires will be sent by Castor EDC, in which the results also will be recorded (13). Furthermore one and two years after surgery telephone call is conducted to assess post-operative complications such as testicular atrophy and recurrence. Prior to the telephone consult, parents are asked to send a photo to the researcher with the help of a secured online application (SURFfilesender) and a coded number

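### Read literally, the complication endpoint omits visceral injury, umbilical port-site hernia and deep infection, events that bear more on the arm that enters the abdomen

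*Protocol*

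**What the plan says.** Section 8.1.2 of the protocol gives the complication endpoint in two bracketed lists, each opened with *i.e.*:

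- Operative: "Operative (i.e. injury of spermatic vessels or spermatic cord, tuba lesions, bleeding and apnea".
- Postoperative: "hematoma/scrotal edema, hydrocele, wound infection, iatrogenic ascent of the testis, testicular atrophy and ileus) within one year after primary surgery".

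The Definitions that follow describe wound or surgical site infection as "Infection, occurring within 30 days of surgery, involving only the skin and subcutaneous tissue", with further conditions on discharge or culture and on local signs.

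The two operations differ in access. For PIRS (section 5.1), "Pneumoperitoneum is established by introducing a 3-5-mm reusable trocar through a sub-umbilical incision", and a needle is then passed through the abdominal wall into the cavity. For open repair (section 5.2), "an incision is made in a skin line in the groin".

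Data collection is worded differently from the endpoint. Under section 8.3, "perioperative complications of surgery (iatrogenic injury, apnoea) will be recorded in Case Report Forms". Section 9.2.1 records all adverse events up to the four-week contact, on the ground that none occur later. Section 12.1 has a third, shorter list: wound infection, testicular atrophy, apnoea and recurrence. Section 10.2 compares peri- and post-operative complications between arms in a 2x2 table with a chi-square test and does not say which list feeds it.

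**The concern.** A complication comparison is only as fair as its list of events. If the list leaves out a type of harm that one technique is more exposed to, that technique's complication count is understated and no later analysis can recover it.

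PIRS requires abdominal entry and open repair does not plan it, so injury to a viscus, a hernia at the umbilical port and infection below the subcutaneous layer are events one would expect to see named. The protocol is aware of visceral injury: the introduction says intra-corporeal laparoscopy "carries a higher risk for iatrogenic visceral injury following the many manipulations with instruments in the peritoneal cavity" and uses this as part of the case for PIRS. It does not then list the event in the endpoint.

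Complications are a secondary endpoint with their own test, they enter the cost analysis, and fewer complications is one of the potential advantages of laparoscopy named in the rationale. What is at stake is mainly that a few serious events could be absent from the complication table.

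**Working it through.** **Step 1. Each event against each route in the protocol.**

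| Event | Endpoint list, 8.1.2 | Other record | Clearly in the 10.2 comparison? |
|---|---|---|---|
| Bowel or bladder injury | Not named | Iatrogenic injury on the CRF (8.3); AE/SAE to four weeks (9.2) | No |
| Deep or intra-abdominal infection | Fails the infection definition, either arm | AE/SAE to four weeks | No |
| Umbilical port-site hernia, early | Not named | AE to four weeks | No |
| Umbilical port-site hernia, after four weeks | Not named | No clear route | No |
| Bleeding from a major vessel | Covered: bleeding has no limit of site | Also AE/SAE | Yes |
| Ileus | Named | Also AE/SAE | Yes |

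On late port-site hernia: adverse-event recording has stopped. The photograph requested under section 3 is of the groins and serves to score testicular atrophy, recurrence and contralateral hernia. The one- and two-year calls in section 8.3 give testicular atrophy and recurrence as their examples. The primary endpoint in section 8.1.1 counts reoperation for ipsilateral recurrence or contralateral inguinal hernia only.

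**Step 2. The plan's own figures.** The protocol gives no expected rate for complications, so there is none to reproduce. Its sample size belongs to the primary endpoint (6% v 1%). With the pooled formula, n = [1.96·√(2·0.035·0.965) + 0.842·√(0.06·0.94 + 0.01·0.99)]² / 0.05² = 211 per arm, or 422 in total, as stated. Nothing in this point changes it.

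**Step 3. How many events could be missed.** Enrolment is 464 at 1:1, so 464/2 = 232 children per arm. Let p be the rate of uncounted events per PIRS child. The value of p is an assumption. Expected number = 232·p; chance of at least one = 1 − (1 − p)^232.

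| Assumed p | Expected uncounted | Chance of at least one |
|---|---|---|
| 0.1% | 0.23 | 21% |
| 0.25% | 0.58 | 44% |
| 0.5% | 1.16 | 69% |
| 1% | 2.32 | 90% |

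**Step 4. Effect on the test.** Suppose, again as an assumption, that the true complication rate is 5% in both arms and that some percentage points of PIRS events are uncounted, with none uncounted in the open arm. With 232 per arm and two-sided alpha 0.05, the chance of a significant result in favour of PIRS is:

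- nothing uncounted: 2.5%
- 0.5 points uncounted: about 4%
- 1 point uncounted: about 7%
- 2 points uncounted: about 19%

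Setting the open-arm omission to zero makes this an upper illustration, because the infection definition also drops deep groin infections after open repair.

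**The case against.** The strongest reply has four parts.

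1. **The lists may be examples.** The protocol uses *i.e.* loosely: section 8.3 applies it to an 18 gauge needle, while section 5.1 allows 16 or 18 gauge. Section 10.2 does not restrict itself to the 8.1.2 lists. This stands in part: closure is the literal reading, not a certain one. The loose reading leaves its own gap, because the event set would then be decided without a stated rule by staff who know the allocation (section 8.2). The infection limit does not depend on *i.e.* at all.

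2. **Early serious events are recorded.** This stands. Iatrogenic injury goes on the CRF, and all AEs and SAEs are recorded in both arms for four weeks. Section 9.4 even contains a line that SAE reporting runs to the end of the study, which does not agree with the four weeks in section 9.2.2. Elective admissions are excluded from SAEs, so an electively repaired port-site hernia would not be picked up that way. The remaining gap is in what is compared, and in late events.

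3. **The list is not confined to the groin.** A reader might infer that it holds only groin and testicular events plus superficial infection. It does not: bleeding, apnoea, tuba lesions and ileus are there. Nor are the listed events specific to open repair; section 5.1 itself takes care to avoid the vas deferens and testicular vessels during PIRS.

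4. **The introduction's remark on visceral injury concerns intra-corporeal techniques.** This is correct. It is used to set PIRS apart as safer, so it cannot be cited as naming a PIRS hazard. It shows only that the protocol knows the event, and a lower risk is not a zero risk.

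**Conclusion.** The point holds in a limited form. As literally written, the compared endpoint omits visceral injury and umbilical port-site hernia, and the infection definition excludes deep and intra-abdominal infection in both arms. Because only PIRS plans abdominal entry, the omissions plausibly understate PIRS complications more than open ones.

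Two stronger readings are not supported. The first is that the comparison is shown to favour PIRS: the direction is plausible, but there are no rates, and the infection limit also removes events from the open arm. The second is that a bowel injury would vanish from the trial: it would be recorded, though its place in the section 10.2 table is unclear.

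The size rests entirely on assumed rates. At 0.1% to 1%, about 0.2 to 2.3 PIRS events would be uncounted, and at up to 1 point the chance of a false result for PIRS rises from 2.5% to at most about 7%. The effect on the test is probably small. The reason to act is that the few events concerned may be serious and the change is easy. It is a cheap improvement.

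**What to change.** - Write one complication list, identical for both arms, and use it in sections 8.1.2, 8.3, 10.2 and 12.1. State that it is the set of events entering the 2x2 table.
- Add visceral injury (bowel, bladder), umbilical port-site hernia, and deep or organ-space infection. A separate major-vessel item is largely redundant, since bleeding is already listed without limit of site.
- Remove *only* from the infection definition, or classify infection as superficial, deep or organ-space and count all three.
- Ask about the umbilical site at the one-year call, so that a late port-site hernia is captured within the endpoint's one-year window.

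The cost is protocol wording, a few CRF fields and one question at a call that is already planned. The sample size does not change. The downside is a possibly slightly higher reported complication rate.

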#### Definitions

*Testicular atrophy*: Complete testicular atrophy: no palpable testicular tissue in scrotum.

*Partial testicular atrophy*: Testis documented to be smaller at follow-up than at time of inguinal hernia repair.

*Wound infection/Surgical site infections*: Infection, occurring within 30 days of surgery, involving only the skin and subcutaneous tissue. Purulent discharge or organisms isolated from aseptically obtained wound culture must be present. Also at least one of the following signs of infection must be present: Pain or tenderness, localized swelling and redness or heat.

*Apnoea*: An unexplained episode of cessation of breathing for 20 seconds or longer, or a shorter respiratory pause associated with bradycardia, cyanosis, pallor, and/or marked hypotonia.

Total duration of surgery (including anaesthesia) related to primary open or laparoscopic inguinal hernia repair.

Postoperative pain measured according to the children and infants post-operative pain score (CHIPPS) and VAS and pain medication requirement related to post-operative pain within 2 weeks after primary operation.

Length of hospital stay related to inguinal hernia within one year after primary operation.

Time to full recovery within one year after primary operation.

CPPV rate during laparoscopic contra-lateral exploration in the PIRS group. When seen, the CPPV will be corrected.

MCIH rate within one year after primary operation.

Cosmetic appearance scored on a 5-Likert scale from 1-5 (1= bad, 2=unsatisfactory, 3=satisfactory, 4=good, 5=excellent) within one year after primary operation. Cosmetic appearance will be scored 4 weeks and 1 year after primary surgery.

Cost-effectiveness will be assessed from a societal and health care perspective and will include cost of surgery, hospitalization, control visits, re-operation, complications and loss of productivity of the parents/caretakers. Most data will be registered in the medical records; specific data entry forms will be used. Data on productivity loss will be collected by online questionnaires before surgery, four weeks after surgery, one year after surgery and in case of a recurrence or MCIH, four weeks after re-operation. Cost of the operation will be measured using a bottom-up micro costing approach. Other costs will be valued using guideline prices.

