### **3. STUDY DESIGN**

A randomized controlled trial will be performed and 464 infants with a primary unilateral inguinal hernia will be randomized to either open repair or laparoscopic PIRS repair. All operations will be performed by experienced (laparoscopic) paediatric surgeons.

One and two years after surgery all children will be called by the researcher. Prior to this call, patients or their parents will be asked to send a photo of the subject groins.. The latter is done to score testicular atrophy, recurrence or contralateral hernia. This will also be scored during a video call two years post-surgery. It is not possible to blind children or their parents/caretakers or health care professionals for the study arm, since different scars will develop and instructions have to be given for the postoperative treatment of the wound(s).

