### **4.3 Exclusion criteria**

A potential subject who meets any of the following criteria will be excluded from participation in this study: Children with 1. incarcerated inguinal hernia, which have to be operated immediately, 2. recurrent hernia 3. ventricular-peritoneal drain, 4. non-descended testis, 5. parents who are not able to understand the nature or consequences of the study.

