### 10.2 Secondary study parameter(s)

Mean differences and corresponding 95% confidence intervals will be calculated for postoperative pain, duration of hospital admission, time to full recovery and cosmetic appearance. Logistic regression analysis will be performed to adjust for possible confounders (i.e. prematurity, side of inguinal hernia), if necessary. Peri- and post-operative complications will be analysed in a 2x2 contingency table and the data will be assessed by a Chi-Square test. The CPPV rate will only be analysed for the laparoscopic group, since the open repair does not allow for contra-lateral exploration.

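### Complete testicular atrophy is judged only by what can be felt in the scrotum, so a viable testis that has ascended wholly out of it also qualifies

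*Protocol*

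**What the plan says.** The postoperative complications in section 8.1.2 of the protocol include "iatrogenic ascent of the testis, testicular atrophy and ileus", so ascent and atrophy are two items on one list. The Definitions that follow split atrophy in two. The complete form is "Complete testicular atrophy: no palpable testicular tissue in scrotum". The partial form is "Testis documented to be smaller at follow-up than at time of inguinal hernia repair". Ascent has no definition.

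On measurement, section 8.3 has the surgeon record "Preoperative size of both testes". For later follow-up it says: "Furthermore one and two years after surgery telephone call is conducted to assess post-operative complications such as testicular atrophy and recurrence". Section 3 adds a photo of the groins sent before the call, with the stated purpose "The latter is done to score testicular atrophy, recurrence or contralateral hernia", and a video call at two years. Section 10.2 gives the analysis: "Peri- and post-operative complications will be analysed in a 2x2 contingency table", with a chi-square test.

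**The concern.** The criterion for complete atrophy describes where nothing is felt, not whether the testis still exists. Two different events leave the scrotum empty: the testis has been lost, or it is viable and has moved out. The first is permanent loss of an organ. The second is a malposition, which the protocol itself treats as a separate complication. A definition that cannot tell them apart can report malposition as loss.

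The comparison of harms between open repair and PIRS is one of the trial's secondary aims. Where an outcome is rare, a few wrongly classified cases can change how its line in the safety table reads.

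**Working it through.** No arithmetic settles this. The check is to apply the written definitions to each state a testis could be in at follow-up, and then to see whether any other section corrects the result.

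| State at follow-up | Meets the complete-atrophy wording? | Intended category |
|---|---|---|
| Testis lost, nothing to feel | Yes | Complete atrophy |
| Viable testis, normal size, wholly outside the scrotum | Yes | Ascent |
| Testis wholly outside the scrotum and documented smaller | Yes | Ascent and partial atrophy |
| Testis ascended but still felt in the scrotum | No | Ascent |
| Testis in the scrotum, documented smaller | No | Partial atrophy |

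Rows two and three go wrong; the others do not.

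Sections that might correct rows two and three:

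- **Section 4.3** excludes "4. non-descended testis" at entry. This removes malposition before surgery. It does not deal with ascent after surgery.
- **Section 8.3** records testis size before surgery. This helps with partial atrophy once the testis has been found. It records nothing about position.
- **Sections 3 and 8.3** name atrophy as a purpose of the photo and the calls. Ascent is not named. The one- and two-year contacts are by telephone, photo and, at two years, video. The protocol describes no hands-on examination at those times, although the atrophy definition depends on palpation.
- **Section 12.1** names four complications among the data to be collected. Atrophy is one of them and ascent is not.
- **Section 9.2.1** stops adverse-event recording at four weeks, so that route would not pick up ascent first noticed later.

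None of these defines ascent, requires the testis to be located, or sets an order between the two categories.

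The effect on the count can be written in symbols. Let A be the testes truly lost, F the viable testes wholly outside the scrotum, and s the share of F that assessors separate by their own judgement. Then

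counted complete atrophy = A + (1 − s) × F.

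The excess is (1 − s) × F. The protocol gives no value for A, F or s, nor the share of boys, so no figure follows.

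Reach of the error: the primary endpoint (section 8.1.1) is reoperation for recurrence or contralateral hernia, and the sample size (section 4.4) rests on contralateral hernia rates of 6% and 1%. Neither uses testis status. Section 10.2 does not say whether its table is drawn up per complication or per child with any complication. In a per-child table, a boy with ascent counts once either way. In a per-complication table, the atrophy line changes.

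**The case against.** The best defence is that a clinician would not call a normal testis felt in the groin atrophied. The criterion stands under the term testicular atrophy, ascent has its own entry on the list, preoperative size is recorded, and the photo covers the groins. The list in section 8.3 is also introduced as examples, so it does not rule out asking about ascent. This stands in part: misclassification is possible, not shown to be systematic. But the separation would rest on judgement that the protocol does not write down, made by assessors who know the allocation (section 8.2) and who, at one and two years, work without a described physical examination. A photo of the groins does not supply palpation.

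Three stronger readings are tempting, and the documents do not support them.

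- A reader might infer that every ascended testis is counted as atrophy. Only one lying wholly outside the scrotum meets the wording.
- A reader might infer that the atrophy rate is inflated several-fold. Any multiple would need rates of ascent and atrophy that the protocol does not give, and would depend on the pair chosen.
- A reader might infer a false difference between arms, because open repair dissects the cord and ends by returning the testis to the scrotum (section 5.2), while section 5.1 describes no such step. The handling does differ, but no section says that ascent is more frequent with either technique, and the definition is the same in both arms. A difference in full ascent would carry over into the atrophy count; whether there is one is unknown.

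**Conclusion.** The point holds in a limited form. The stated rule gives the wrong category when followed literally: a viable testis that has ascended completely out of the scrotum qualifies as complete atrophy. This is a definition fixed badly in the protocol, not a detail left for a statistical analysis plan.

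The error can only raise the count of complete atrophy. Its size cannot be computed from the documents. It touches one component of a secondary safety endpoint, in boys only. The conclusion assumes that the definition is applied as written; to the extent that assessors locate the testis and use the ascent category, the excess shrinks. The overlap in wording is certain. Its practical weight is not known, but correcting it is cheap enough that the weight need not be known first.

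**What to change.** In section 8.1.2:

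- State that complete atrophy requires both that no testicular tissue is present in the scrotum and that no testis is known or found outside it.
- Define iatrogenic ascent, and score a testis located outside the scrotum as ascent and not as complete atrophy.
- Keep partial atrophy available for that testis if it is documented to be smaller than at repair. A rule of ascent only would hide a testis that has both moved and shrunk.

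In sections 8.3 and 12.1, add ascent to the complications recorded at follow-up. Where remote follow-up reports an empty scrotum and the medical record does not give the location of the testis, record an empty scrotum of undetermined cause instead of complete atrophy, and report the number of such cases by arm.

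The cost is a few sentences, two options on the follow-up form and notification of the amendment under section 12.3. It needs no added visits or patients, because it does not presume an examination that the protocol does not plan. The downside is that a few cases may remain unclassified.

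### Testicular atrophy is defined by palpation or testis size but assessed by phone and photo, and two-week pain has no scheduled assessment between discharge and week four

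*Protocol*

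**What the plan says.** **Atrophy.** Section 8.1.2 lists testicular atrophy and iatrogenic testicular ascent as separate postoperative complications, both counted within one year of surgery. The definitions that follow give the complete form as "Complete testicular atrophy: no palpable testicular tissue in scrotum" and the partial form as "Testis documented to be smaller at follow-up than at time of inguinal hernia repair". Section 8.3 provides the baseline: the list of items that the surgeon enters on the case report form opens with "Preoperative size of both testes, the number of operations per infant". For follow-up, the same section says that "one and two years after surgery telephone call is conducted to assess post-operative complications such as testicular atrophy and recurrence". Section 3 adds that before the call "patients or their parents will be asked to send a photo of the subject groins", that this photo serves to score atrophy, recurrence and contralateral hernia, and that a video call at two years scores them again.

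**Pain.** Section 8.1.2 measures pain by CHIPPS and VAS, together with "pain medication requirement related to post-operative pain within 2 weeks after primary operation". Section 8.3 states "One telephone call is performed by a member of the research team after four weeks", to ask how the child is recovering, about the wound and about recurrence. Online questionnaires go out before surgery, at four weeks and at one year, on the child's health and on economic items. Section 9.2.1 also treats week four as the first follow-up. Section 10.2 plans mean differences with confidence intervals for pain.

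**The concern.** The atrophy definitions call for a hand or a measurement, and the stated follow-up supplies neither. What is recorded would be an impression from a photo or a parent's report, carried under the name of a finding that needs an examination. The complete definition also does not exclude a testis that has moved out of the scrotum, so one event can be counted as ascent, as atrophy, or as both.

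Atrophy is a relevant harm in both arms. Section 5.1 describes leaving a small space to protect the vas and testicular vessels during suturing, and Section 5.2 describes dissecting them off the sac. Under Section 8.2 participants and investigators know the allocation, so errors in remote scoring or in recalled pain could differ between arms.

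For pain, the endpoint window closes before the first scheduled contact after discharge. Section 8.3 names no assessor, form or time point for it.

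**Working it through.** The check is mainly a comparison of definition with schedule.

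**1. Atrophy: what is needed and what is planned**

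| Definition (8.1.2) | Needs | Planned within one year (3, 8.3) | Can it establish the event? |
|---|---|---|---|
| Complete | Palpation of the scrotum | Call and groin photo at one year | No |
| Partial | A follow-up size to set against the preoperative size | Call and groin photo at one year | No; no postoperative size is scheduled |

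The video call comes at two years, after the one-year window, and is also remote. Adverse event recording ends at four weeks (9.2.1). Control visits appear only as a cost item in 8.1.2, with no timing or examination. Scheduled testis examinations within one year: 0.

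**2. Overlap.** An ascended testis leaves no palpable tissue in the scrotum, so it meets the complete-atrophy wording, although ascent is its own item in the same list.

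**3. Pain: timing.** The window closes at 2 × 7 = 14 days. The first scheduled contact is at 4 × 7 = 28 days. The gap is 28 − 14 = 14 days. Scheduled contacts after discharge and inside the window: 0.

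**4. The protocol's own figure.** Section 4.4 gives 422 evaluable children for 6% versus 1%, power 0.80, two-sided alpha 0.05. With pooled variance under the null and no continuity correction:

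n per arm = [1.960 × √(2 × 0.035 × 0.965) + 0.842 × √(0.06 × 0.94 + 0.01 × 0.99)]² / 0.05² = 211 after rounding up, so 2 × 211 = 422.

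The figure reproduces. It concerns the primary endpoint and is used below only as a denominator.

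**5. Illustrations; every rate here is assumed, none is in the protocol**

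- *If* all 211 children in an arm were counted as free of atrophy, the rule of three would give an upper 95% limit of 3/211 = 1.4%. That denominator includes girls. For boys only it is 3/(211 × share of boys), which is larger; the protocol does not give the share.
- At an assumed true rate of 1%, the expected number is 211 × 0.01 = 2.1 events per arm, again with girls in the denominator.
- Recorded rate = true rate × sensitivity + (1 − true rate) × (1 − specificity). At a true rate of 1%:
  - sensitivity 0.5, specificity 1.00: 0.01 × 0.5 = 0.5%
  - sensitivity 0.5, specificity 0.98: 0.005 + 0.99 × 0.02 = 2.5%
  - over sensitivity 0.3 to 0.9 and specificity 0.95 to 1.00: from 0.01 × 0.3 = 0.3% to 0.009 + 0.99 × 0.05 = 5.9%

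The direction of the error is therefore not fixed: remote scoring could understate or overstate atrophy.

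**The case against.** **Coding of unexamined boys.** A reader might infer that boys who are not examined will be entered as having no atrophy, so that the report gives false reassurance. The protocol contains no such coding rule, and Section 10.1 plans multiple imputation for missing values. This objection stands in full.

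**Other sources of testis findings.** Section 8.1.2 mentions control visits and data from medical records, and a testis documented as smaller could be found in a record. A one-year call might also pick up a diagnosis made elsewhere. This stands in part. The mentions are in the costing paragraph, give no timing or examination, and do not alter the statement that the photo and the call are how atrophy is assessed.

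**Pain.** A reader might infer that two-week pain would be missed altogether. The documents do not support that. The child is in hospital at the start of the window, where CHIPPS or VAS could be scored, and the four-week questionnaire could ask about the preceding weeks. The two-week limit may also attach only to analgesic need. What remains is that the protocol assigns neither route to pain, and that any information about the days after discharge would be recall.

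**Size.** The 1% rate is assumed and the 211 includes girls. At about two events per arm, even complete examination would not support a comparison of arms. This stands: the issue is the validity of what is reported, not lost power.

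**Remedy.** Counting only atrophy found in records, without adding an examination, would select boys with complaints. This stands, and the fix must say so.

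**Conclusion.** The concern holds for two secondary endpoints. For atrophy, the protocol names a method that cannot establish the event it defines, schedules no testis examination inside the one-year window, and lets ascent count as complete atrophy. This is a contradiction between stated definitions and a stated method, not detail left for a statistical analysis plan. For pain, the narrower conclusion is that nothing is scheduled from discharge until week four, 14 days after the window closes, so post-discharge pain and analgesic data would rest on recall at best.

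The conclusion rests on the protocol's definitions and schedule alone. It does not depend on the 1.4% or 1% figures or on the misclassification range, which are illustrative. The primary endpoint, reoperation, and the sample size are unaffected. The point should be corrected, but it does not threaten the main result.

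**What to change.** Reconcile definition and method in Sections 3, 8.1.2 and 8.3:

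- **Separate ascent.** Exclude an ascended testis from atrophy and record it under its own heading.
- **Name remote findings for what they are.** Report the photo, call or video result as visible or parent-reported asymmetry, distinct from atrophy confirmed at any physical examination in the medical record.
- **Show the denominator.** Record boys not examined as 'not assessed', report the number of boys examined per arm, and state that they are a selected group. Exempt confirmed atrophy from the multiple imputation in Section 10.1, since imputing from selected boys would carry their rate over to the others.
- **Time the pain items.** Send the pain and analgesic items through the existing Castor questionnaires inside the two-week window.

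The cost is new wording in the definitions and case report form, and one additional automated questionnaire. The downside is that few boys will be evaluable for confirmed atrophy, so the trial should draw no between-arm conclusion on it. No extra visit is required, and the sample size does not change.
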